## Abstract

**Background::**

Despite that the urge urinary incontinence (UUI) is a nonfatal disease, it can lead to anxiety, embarrassment and depression to the patient. UUI is a common public health problem that can significantly affect the quality of life of the patient. Several conservative treatments have been recommended for the treatment of UUI; however, their efficiency remains unclear, leaving the disease without a real effective treatment. The clinical application of acupuncture to treat UUI is currently considered an effective approach despite the limited evidence that support its efficiency. The aim of this study is to assess the efficacy and safety of electroacupuncture therapy in the treatment of UUI.

**Methods and analysis::**

A randomized, parallel, controlled study will be performed. Patients with UUI treated with electroacupuncture group (EA) will compare with the sham-treated sham EA (SA) patients. A total of 100 participants with UUI will be randomly allocated to either the EA or the SA group with a 1:1 ratio. The treatment of UUI patients will performed 3 times per week, for 8 weeks in 30-minute sessions. At the end of the treatment the patients will be followed-up until week 32. The primary outcomes include scores of incontinence questionnaire-short form, the average 24-hour urgency incontinence episodes, and the average 24-hour urge episodes responses from baseline until the 4th, 8th , 24th, and 32nd week. The secondary outcomes included the average 24-hour urine volume and the average 24-hour micturition frequency responses from baseline until the 8th and 32nd week, as well as the change in incontinence quality of life scores from baseline at the 8th and 32nd week. In addition, the degree of satisfaction of the participants undergoing acupuncture treatment will be measured at the 4th and 8th week. The participants’ clinical acupuncture expectations were evaluated at baseline, and the questionnaire for urinary incontinence diagnosis was used to identify stress incontinence, mixed urinary incontinence, and urge incontinence at baseline.

**Discussion::**

This is a randomized, controlled, observer-blinded trial of electroacupuncture treatment for UUI. The results of this trial will provide more evidence on whether electroacupuncture is efficacious for treating UUI.

Advantage and Disadvantage(1)Through previous studies, electroacupuncture for UUI has been proved effective. However, there is still a lack of research on the treatment of UUI with electroacupuncture and sham electroacupuncture.(2)This trial will assess the efficacy and safety of electroacupuncture in the treatment of acute UUI and will provide high-quality, current evidence for patients and clinicians seeking safe and effective treatments.(3)In this study, we evaluated the safety of patients and clinical expectation of acupuncture, which was not common in previous studies.(4)There might be an overestimation of the electroacupuncture effect due to the small sample size of this trial.

## Introduction

1

According to the International Continence Society (ICS), urge urinary incontinence (UUI) is defined as the complaint of involuntary loss of urine associated with urgency.^[1,2]^ It is characterized by a sudden compelling desire to pass urine that is difficult to defer.^[3]^ UUI often leads to a severely degraded quality of life due to the associated symptoms such as urgency, frequent urination, and urinary incontinence. In addition, it can lead to psychological problems such as depression and anxiety.^[4]^ UUI affects millions of men and women worldwide, which raises huge economic and social burden.^[5]^ Epidemiological investigation have shown that the prevalence of UUI is between 1. 5% and 36. 4%,^[5,6]^ and the incidence increases with age.^[7]^ It is closely related to gender, race, age, BMI, history of mental illness (including depression), pelvic organ prolapse,^[8]^ lifestyle, and other complications such as high blood pressure, diabetes, cancer, lung disease, heart disease, arthritis, and stroke.^[9]^ The association between weight and the UUI subtype in young/middle-aged women was reported to increase 6-fold when the body mass index was greater than 35 kg/m^2^.^[10]^

Currently, the guidelines^[11]^ for UUI treatment recommend behavior therapy as the first-line therapy, such as bladder training, electrical stimulation, pelvic floor muscle training, and biofeedback therapy. In addition, lifestyle changes include the management of caffeine intake, weight, fluid and diet. Drugs are considered the second-line therapy for UUI, which include oxybutynin, Propiverine, Solifenacin, Tolterodine, Trospium.^[11]^ The third-line therapy includes surgery treatment, botulinum toxin type A injection, the use of 5-hydroxytryptamine receptor blockers, and neuromodulation. The currently recommended treatment is a combination of behavioral therapy and medication. However, a study^[12]^ have shown that behavioral therapy often takes weeks or months to achieve satisfactory results, while compliance is not high in most patients. In addition, it has been shown that drug therapy may lead to some side effects, such as dry mouth, which is the most common side effect, as well as blurred vision, constipation, fatigue and cognitive impairment.^[13]^ Surgery, on the other hand, is also associated with certain adverse reactions.^[14,15]^ Therefore, the clinical application of the current UUI treatments remain limited due to these complications.

Acupuncture is a valuable heritage in the Chinese culture and is considered a scientific tradition. It has the advantage of remarkable curative effects, simple operation procedure, low price and few side effects. Many studies have recently attempted to use acupuncture for UUI treatment and adjuvant therapy, and a large number of clinical studies have reported beneficial clinical effects of acupuncture in improving urinary incontinence and urinalysis in UUI patients.^[16–29]^ However, the evidence remain weak due to the lack of long-term follow-up periods, insufficient sample size, and low quality of related studies, which raises the need for more clinical trials to prove that acupuncture may be an optional treatment for UUI in the future. Therefore, we designed this trial to further assess the efficacy of electroacupuncture for treating UUI. The results of this trial will provide a more scientific evidence for a safe, effective and easy-to-promote treatment for UUI in the future.

## Methods

2

### Study design

2.1

This is a randomized, controlled, observer-blinded trial that included 2 parallel groups with a 1:1 allocation ratio. Figure 1 shows the study flowchart.

**Figure 1 F1:**
[figure not shown]
Flowchart of the study design.

### Participants and recruitment

2.2

A total of 100 participants will be recruited between January 2020 and March 2021 through the Second Affiliated Hospital of Guizhou University of Traditional Chinese Medicine website or via public posters. A researcher is responsible for the recruitment and screening of participants, and a urologist is responsible for the diagnosis. A 2-week baseline assessment will be conducted by the researcher, which will be responsible for assessing and recording the participants’ baseline status. After signing a written informed consent, eligible participants will be assigned with random numbers generated by a third party.

### Randomization and allocation concealment

2.3

The third party will be responsible for randomly grouping the participants and is strictly prohibited to participate in the treatment and data collection during the process. The random grouping is produced using the statistical product and service solutions 22. 0 (SPSS) software, and the final group assignments will be sealed in opaque envelopes. All the envelopes were numbered in the order of the sequence numbers of enrolled cases entering the clinical trial. Hence, the group assignment will be sealed inside and the sequence numbers will be printed on the outside of the opaque envelope. In addition, the acupuncturist will transfer the information of the information of random number and group assignments to each patient by phone or email.

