### Blinding

2.4

Owing to the particularity of clinical acupuncture and moxibustion, it is impossible to use a strict standard blind method for evaluation. Thus, a third party that is blind to the grouping condition carried out the effect evaluation. The efficacy evaluator, the operator and the statistician will be carried out by independent researchers. Subjects, efficacy evaluators, and statistical analysts will be all blinded.

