### The electroacupuncture group (EA)

4.1

Acupuncturists with more than 2 years of clinical experience, who have obtained the Chinese licensed physician certificate, are responsible for performing the acupuncture. The choice of intervention plan and acupoint is based on the expert's experience and based on previous studies.^[21,30–32]^ The acupoints of Ciliao (BLadder [BL]32), Zhongliao (BL33) and Huiyang (BL35) will be used (Table 1). All acupoints will be localized according to the name and location of acupoints drafted in 2006 by the National Standard of the People's Republic of China (GB/T 12346–2006). The electric stimulators (SDZ-V electroacupuncture apparatus), and stainless-steel sterilized needles (Huatuo disposable acupuncture needle; 0. 3 mm×50 mm/0. 3 mm×75 mm), were all purchased from the Suzhou Medical Appliance Factory of China. The electric stimulators will apply to the EA and to the sham electroacupuncture group (SA). During the treatment, participants will lie in the prone position, and the acupuncturists will use cotton balls soaked with 75% alcohol to sterilize the skin at the acupuncture site. After skin disinfection, sterile stainless-steel needles will be inserted into the selected acupuncture points. The needles are inserted approximately 50 to 60 mm into the skin with an angle of 60° in an inferomedial direction for BL32/BL33 and a slightly superolateral direction for BL35. After the insertion of the needle, for all needles perform small, equal manipulations of twirling, lifting, and thrusting to reach de qi (these sensations are composed of numbness, soreness, heaviness and swelling), it is considered to be an important component of acupuncture and moxibustion.^[33]^ Paired electrodes from the electroacupuncture apparatus were laterally connected to the needles’ handles of the bilateral BL32, BL33 and BL35. Acupuncture points are continuously stimulated with 100 Hz wave and a 1 to 5 mA electric current for 30 minutes. It is best to make the skin around the acupoint tremble slightly without pain. Participants were treated 3 times a week (every other day) for 8 weeks, with a total of 24 times, and 24 weeks of follow-up after treatment. The fixing pads are placed on the acupuncture points to keep the participants in a blind state.

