### The SA group

4.2

The selected non-meridional and non-acupoint points are 20 mm from the level of BL32, BL33 and BL35, and the selected acupoint are away from the second lateral line of the Bladder Meridian (Fig. 2). During the treatment, participants will lie in the prone position, the skin is disinfected as in the EA group, and the fixation pad is attached to the acupuncture point. A 1.5-inch blunt needle (from Suzhou Medical Appliance Factory of China) is used to puncture through the fixed pad into the skin surface, then evenly twisted and turned, however, without piercing the skin. Paired electrodes from the electroacupuncture apparatus were laterally connected to the needles’ handles of the bilateral sham acupoints. The dedicated power supply cord is cut off, but the appearance is as usual; that is, the electroacupuncture indicator is on, but is actually not powered on. The frequency is 5 Hz and a current intensity of 0.1 to 0.5 mA. The treatment time, waveform and SDZ-V electroacupuncture apparatus are the same as those used for the EA group. The patients are told that it an effective slight current input will be applied that may not result in a sensation of stimulation. The treatment of the 2 groups of participants will be carried out separately in different rooms to avoid communication between the participants. At the end of the trial, participants were given 10 times free compensatory treatments.

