### Primary outcomes

5.1

a.The primary outcome measure is the score change in incontinence questionnaire-short form (ICI-Q-SF).Questionnaire ICI-Q-SF, scores ranging from 0 to 21, with higher scores indicating greater impairment, are compared with the baseline at the 4th (during treatment), 8th (after treatment), 24th (the first follow-up), and 32nd (the second follow-up) weeks of the study.ICI-Q-SF is the world's first universal incontinence assessment scale.^[34]^ which is mainly used to assess the frequency of incontinence, the causes of incontinence, and the impact of incontinence on the quality of life. Participants answered 4 questions related to symptoms based on their urination experience in the last week before the test. This includes the number of urine leaks, the amount of urine leakage, the impact of urine leakage on daily life, and when it occurs. The answers are recorded as 0 to 5 points, 0 to 6 points, 0 to 10 points, and the total score between 0 and 21 points. There is 1 unscored question, and the scale Cronbach's alpha coefficient was 0.92.^[34]^ The table is recommended as grade A by the Canadian urological association and the international urinary incontinence advisory committee, and as grade B by the European urological association. It is also recommended for the quantification of the severity of urinary incontinence by the UK's national institute of health and clinical excellence.b.The change in the average 24-hour urgency incontinence episodes, compared with the baseline and at the 4th, 8th, 24th and 32nd week.The 3-day urination diary is another valid, reliable and sensitive measure for patients with UUI. It has been translated into several languages, including Chinese, and is widely used in clinical records to indicate the number of urination during the day, nocturia, urgency, and urgency incontinence, as well as the amount of urine per urination and the amount of drinking water.^[35]^c.The change in the average 24-hour urge episodes, compared with the baseline and at the 4th, 8th, 24th, and 32nd week.

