Finally, a 24-week follow-up period (9–32 weeks) is established to observe the sustained effect of electroacupuncture on UUI patients after the end of the treatment sessions. However, certain limitations are associated with this study that require to be mentioned. Owing to the characteristics of acupuncture, it is hard to blind the acupuncturists and patients. Therefore, the randomization process is tightly controlled so as to minimize the possible bias between the 2 treatments. In addition, the investigators and data analysts are also blinded. Furthermore, there might be an overestimation of the electroacupuncture effect due to the small sample size of this trial. In summary, this study can lay the foundation to design larger randomized controlled trials in the future. The results will provide more reliable evidence and elucidate the value and effectiveness of electroacupuncture in the treatment of UUI patients.

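### Section 2.3 has the acupuncturist send each patient the group assignment, which contradicts the statement in section 2.4 that subjects are blinded and defeats the sham procedure

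*Protocol article*

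**What the plan says.** Section 2.3 (Randomization and allocation concealment) has a third party generate the sequence and seals the assignments in numbered opaque envelopes. It then says that "the acupuncturist will transfer the information of the information of random number and group assignments to each patient by phone or email".

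Section 2.4 (Blinding) says that "Subjects, efficacy evaluators, and statistical analysts will be all blinded".

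Section 4.1 (electroacupuncture group) gives a blinding device for the active arm: "The fixing pads are placed on the acupuncture points to keep the participants in a blind state". Section 4.2 (sham group) gives the counterpart. A blunt needle is pressed through a pad without piercing the skin, and "the electroacupuncture indicator is on, but is actually not powered on". Sham patients also receive a reassurance: "The patients are told that it an effective slight current input will be applied that may not result in a sensation of stimulation". The two groups are treated in different rooms so that participants do not talk to each other.

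Section 5.1 names three primary outcomes: change in ICI-Q-SF score, in average 24-hour urgency incontinence episodes and in average 24-hour urge episodes. Of the ICI-Q-SF it says "Participants answered 4 questions related to symptoms based on their urination experience in the last week before the test". Under the episode counts it introduces the diary: "The 3-day urination diary is another valid, reliable and sensitive measure for patients with UUI".

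Section 7 (Discussion) lists as a limitation that "it is hard to blind the acupuncturists and patients", and adds that investigators and data analysts are blinded too. The abstract and section 2.1 call the trial observer-blinded.

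**The concern.** The trial exists to separate the effect of electroacupuncture from the response to a convincing imitation. That works only if patients in both arms believe to the same degree that they are receiving active treatment. An instruction to send patients their assignment removes that condition.

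The outcomes make this more serious. An independent evaluator protects an outcome that the evaluator judges. It does not protect one that the patient reports, because the patient's knowledge has already shaped the answer before the evaluator sees it. A patient who knows the treatment is sham may expect less, report less improvement or be less inclined to stay in the trial. A patient who knows the treatment is active may do the opposite. A difference between arms could then reflect expectation, the treatment, or both, and the planned comparison could not tell them apart.

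**Working it through.** No figure in the plan bears on this point, so there is nothing to recompute. The check sets the passages side by side.

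1. **What is sent.** Section 2.3 lists two items, the random number and the group assignment. Because the number is listed separately, the assignment cannot be read as another word for the study number. In the same section the group assignment is what is sealed inside the envelope, that is, the arm.

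2. **To whom.** The recipient is each patient. The sender is the acupuncturist, who has to know the arm to deliver the treatment.

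3. **Is it masked?** No section says that the assignment sent to the patient is coded or hidden.

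4. **Against section 2.4.** A subject who has been told the arm is not blinded. The two statements cannot both be carried out.

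5. **Against sections 4.1 and 4.2.** The pads, the blunt needle, the lit but unpowered device and the separate rooms all serve to stop the patient from learning the arm. If the arm has been communicated by phone or email, none of them can do that. They also show that patient blinding is intended, so section 2.3 is the statement out of line.

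6. **Which outcomes are exposed.** For the ICI-Q-SF, section 5.1 says outright that participants answer it. For the two episode counts, section 5.1 describes a 3-day urination diary that records urgency and urgency incontinence. It does not say in words who fills it in, but completion by the patient is the natural reading. On that reading all three primary outcomes are reported by the person who would be unblinded.

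7. **Would the plan detect it?** The abstract places the measurement of acupuncture expectation at baseline only. Nothing in the article describes a later measure of expectation or of perceived allocation, so the effect of disclosure would not show in the data described.

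8. **Against section 7.** The limitation that patients are hard to blind is only weakly at odds with section 2.4, which itself concedes that strict blinding is impossible before claiming it for subjects. Still, a reader who goes from the observer-blinded label to section 2.4 and then to section 7 cannot tell with certainty whether patients count as blinded.

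**The case against.** The strongest reply is that this is a slip of drafting. The sentence in section 2.3 is visibly garbled, and every other part of the design is built to keep patients blind. On that view the authors meant that patients would receive a number or a coded group. This is plausible, and it is why the point is best described as an internal contradiction rather than a deliberate choice to unblind. It does not remove the point. The sentence is a positive instruction to staff, nothing in the document supports a coded meaning, and no fuller protocol could make both sections true. If staff followed it, the disclosure could not be undone.

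Several stronger readings are tempting and are not supported:

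- **Disclosure before treatment.** A reader might infer this because the sentence stands in the randomisation section. The text gives no time.
- **Different scripts in the two arms.** The reassurance about an unfelt current appears only in section 4.2. A reader might infer that the active arm hears something else. That rests on silence in a condensed article, which commonly leaves participant scripts to the full protocol.
- **A bias as large as the treatment effect.** Section 5.5 cites a 40% reduction under placebo acupuncture and 59% under acupuncture, a difference of 59 − 40 = 19 points. A reader might reason that losing half of the sham response would create 0.5 × 40 = 20 points, or losing a quarter 0.25 × 40 = 10 points. The fractions have no source in the document. The change in a sham arm can also include regression to the mean and natural course, which disclosure would not remove. Section 5.5 is also unclear on whether 40% and 59% are response rates or reductions in episodes.
- **Section 7 flatly contradicts section 2.4.** Hard to blind is not the same as unblinded, and the remark that investigators and analysts are also blinded can be read as in addition to patients.

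**Conclusion.** The point holds as a contradiction that must be corrected. The instruction in section 2.3 cannot be followed while subjects remain blinded as section 2.4 says, and following it would defeat the sham measures of sections 4.1 and 4.2. All three primary outcomes would then be open to expectation bias that a blinded evaluator cannot remove.

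The conclusion rests on two readings. The first is that the group assignment in section 2.3 means the arm, which the wording of that section supports. The second is that patients complete the diary, which is natural but not stated. If the second were wrong, the ICI-Q-SF would still be exposed.

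The size of the bias cannot be derived from the document, and none is claimed. Confidence is high that the texts conflict. The document does not establish that patients would in practice be told plainly that they are in the sham group.

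**What to change.** - **Section 2.3:** replace the sentence on transferring assignments. Patients receive only their study number and appointment. The assignment goes only to the treating acupuncturist.
- **Sections 2.4 and 7:** state in the same terms who is blinded (patients, efficacy evaluators, statistical analysts) and who is not (the treating acupuncturist). If the authors regard patient blinding as imperfect, both sections should say so. The observer-blinded label in the abstract and section 2.1 should then match.
- **Optional:** at week 8, when satisfaction is already assessed, ask each participant which group they believe they were in. This would let readers check the blinding claim. The contradiction can be resolved without it.

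The cost is a change of wording and, if the option is taken, one extra question at an existing assessment. No added visits or staff are needed, and the treatment procedures do not change.
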